## Abstract

Background: Guatemala remains one of the poorest countries in Central America and suffers from high rates of social inequality and violence. In addition to the negative impact that two years without attending school has had on Guatemalan children due to the consequences of the COVID-19 pandemic, this unfavourable socioeconomic context poses a risk to children’s emotional and cognitive development. This work presents a protocol for implementing a cognitive and emotional stimulation program aimed at increasing the academic performance of these children and consequently improving their quality of life. Methods: The protocol proposes the implementation of a randomized controlled trial to assess the efficacy of a 24-session-long stimulation program. It targets the cognitive functions of attention, language, executive functions, and social cognition, using the digital neurorehabilitation platform NeuronUP. The participants (*n* = 480) will be randomly assigned to an Experimental or Control group. Pre- and post-intervention assessments will be carried out, together with a follow-up in the next academic year, in which both groups will change roles. Results will be compared for the first and second years, looking for differences in academic and cognitive performance between groups. Discussion: Mid- and long-term outcomes are still unknown, but effective interventions based on this protocol are expected to facilitate the following benefits for participants: (1) improved cognitive and emotional development; (2) improved academic performance; (3) improved well-being. We expect to create a validated neuropsychological stimulation program that could be applied in similar socioeconomically disadvantaged contexts around the world to help these children improve their life chances.

## 1. Introduction

The pandemic (COVID-19) represented an extreme threat to the advancement of education in Guatemala because of the significant impact it has had at various levels. At a local level, educational centres were closed for almost two years, and more broadly, there has been an economic recession at the national and worldwide levels. The closures within the school system caused a stagnation of learning, along with an increase in school dropouts and a reduction in school attachment [1]. The country’s economic crisis impacted the most vulnerable individuals, directly affecting their quality of life and increasing the inequalities that already exist within the country [2]. Some of the impacts on students and their families, who have been in a forced distance-learning model for the past two years, include worsening nutritional situations (due to the students not being fed at schools), deteriorating mental health (particularly increased anxiety, stress, and burnout symptoms [3,4,5,6]), and a worsening vulnerablity [1]. It is important to mention that child labour, abuse, and unwanted pregnancies are problems that also manifest when schooling becomes home-based [7,8]. Consequently, it is necessary to implement concrete strategies to counteract or lessen the impact of this situation as much as possible, and this is the motivation for developing the following intervention protocol.

Guatemala remains one of the poorest countries in the American continent with high rates of social inequality and violence, in which structural problems such as racial discrimination, gender inequality, extreme poverty and exclusion, an unstable political situation, and an aberrant lack of access to justice constitute obstacles to the full enjoyment of human rights [2]. Additionally, racism and discrimination against indigenous peoples are deeply rooted. The indigenous population faces more unfavourable conditions than the non-indigenous population in terms of access to employment, health, education, as well as average income and rates of extreme poverty [2]. Guatemala is a diverse, multilingual, and multicultural country with 22 language communities. According to data from the last Census [9], the estimated Guatemalan population in 2020 was 16,858,333 inhabitants. The country’s gross domestic product per capita is around 39,043 quetzals, which would correspond to approximately 5 US dollars. It is the country in Latin America with the most chronic child malnutrition and the fourth worldwide, according to data from the World Bank [2]. Of relevance, in terms of the distribution of the country’s inhabitants, half of the population resides in rural areas, where three out of four inhabitants live in poverty [2]. The schools where the intervention will be carried out are in so-called high-risk areas located within the department of Guatemala. These are areas where extreme violence, assaults, murders, and extortion are situations that happen daily, and the risk of dropping out of school is very high due to reasons including lack of money, child labour, or student demotivation [10]. 

Living conditions during childhood and adolescence affect the cognitive and emotional development of minors, resulting in important long-term effects in their adult life [11,12,13,14]. Existing literature on growing up in disadvantaged environments reports that language development, attention, and executive functions can all be affected. Additionally, experiencing these types of adverse contexts can also have a considerable negative impact on children’s social skills and emotional regulation [15,16,17,18]. The development of this study protocol arises from the need to respond to some of the problems discovered after the conclusion of a previous project [19]. Its goal was to improve existing neuropsychological assessment task scores for children and adolescents in Guatemala and study how different factors within their environment could affect their cognitive development. The results obtained in this previous study revealed that Guatemalan children and adolescents participating in the project needed effective support on multiple levels due to their situations of vulnerability. In this study, vulnerability was defined as belonging to an especially disadvantaged socioeconomic context, both in terms of poverty and direct exposure to extreme violence; this was the definition used in the previous study [20]. This showed that the hypotheses regarding the negative impact of growing up in disadvantaged socioeconomic environments (e.g., low educational level of caregivers, little intellectual stimulation in their environment, food insecurity) on the cognitive performance of children and adolescents were confirmed in this population [20]. Additionally, it was possible to detect a series of mental health difficulties in some of the participants that could not be left unattended. This included high levels of anxiety and depression, especially among children from urban areas with high rates of violence [21]. In summary, evidence indicates that living conditions during childhood and adolescence affect the cognitive and emotional development of children, having significant effects on their academic performance, which in turn tends to condition their long-term adult life [12,13,14]. Likewise, the stress associated with poverty causes a serious impact on the emotional and social development of these children, highlighting the urgent need to work in these areas [22,23]. 

Neuropsychological stimulation programs focused on both cognitive and emotional functions have a long tradition in the clinical field, being the treatment of first choice in various neurodevelopmental disorders [24]. These programs are designed to train specific cognitive skills (such as attention, memory, language, etc.), with a wide range of activities, games, and other media, so patients can improve cognitive skills that are not fully acquired/developed (due to neurodevelopmental disorders) or have declined (due to acquired brain damage or degenerative illnesses). In addition, research exists demonstrating the efficacy of neuropsychological interventions focused on specific cognitive domains in non-clinical child populations belonging to socioeconomically vulnerable contexts [25,26,27]. The results suggest that protocols employing different agents and materials in cognitive intervention, with early intervention and a large number of sessions, are the most effective. It has also been shown that children living in socioeconomically vulnerable contexts can also benefit from learning emotional regulation tools to constructively face the various risk situations they are frequently exposed to in their daily lives [28]. Nevertheless, we noted that scientific evidence on the efficacy of neuropsychological stimulation programs for children at risk of social exclusion, and their positive effects on cognitive and emotional skills, as well as their expected impact on academic performance and quality of life, is still somewhat limited [27,29,30].

The previous studies and factors mentioned above have been strong motivation for the development of the following protocol for the neuropsychological stimulation program. The implementation of a neuropsychological intervention program that stimulates both cognitive development (especially those mental functions in which a greater negative impact of the socioeconomic context was detected), as well as emotional skills that reinforce the socio-emotional development of these children (an important protective factor against mood swings and other mental health disorders to which they are frequently exposed) would be greatly beneficial for children living in socioeconomically vulnerable contexts [31,32].

## 2. Materials and Methods

### 2.1. Participants and Study Setting

#### 2.1.1. Participants’ Characteristics

Students from the 5th grade of primary school, from educational centres located in particularly vulnerable areas from Guatemala City’s suburbs, will be invited to participate in the intervention program. The reason for choosing this grade is that the approximate age of the children in this school stage are at the minimum that ensures they have acquired certain skills necessary for adequate participation in the intervention program (e.g., sufficient ability to sustain their attention, reading comprehension, etc.), and therefore, they may benefit more from the proposed intervention. It has been found that this is the optimal educational level for stimulation programs to succeed [33,34]. Most children will be between 10 and 12 years old. However, given the challenging social background and course disruption caused by the pandemic, it is likely that there will be children 1–2 years older in this grade. The following additional inclusion criteria will be considered:-Being a proficient speaker of the Spanish language.-Having acquired sufficient reading skills to understand the activities included in the intervention (percentile score > 5 in the Inter-American Reading Series L-3-DEs).-Having a sufficient level of non-verbal intelligence to understand and interact with the activities included in the intervention (percentile score > 5 in the Non-Verbal Intelligence Test TONI-2).-Not having a diagnosis of serious sensory or motor difficulties, or having insufficiently corrected ones, which would prevent adequate performance in intervention activities.

#### 2.1.2. Recruitment Strategy

Fe y Alegría is an international Jesuit NGO dedicated to creating schools and offering education in socioeconomically disadvantaged areas throughout many Spanish-speaking countries. In Guatemala, they currently have a country-wide network of educational centres, consisting of 46 schools in total. Five centres located in the urban area have been chosen as a sample to represent the total population of their students due to the large logistical challenge of accessing more remote schools and because they have sufficient technical infrastructure (such as adequate Wi-Fi network stability) to carry out the project. Three of the centres are in the suburbs of the Department of Guatemala, and two are in the Municipality of Villa Nueva. All of them are in colonias (neighbourhoods) characterized by low socioeconomic level, aggravated by very high exposure to violence; assaults, deaths, and extortions are daily situations in these communities, which makes them especially vulnerable areas. Between these five centres, there are approximately 1400 5th grade children enrolled. Every child have to provide oral consent to participate in this study, and their legal guardians must sign an informed consent document allowing the use of collected data for research purposes, after being extensively briefed about the goals, methods, and potential benefits of participation (this document was provided by the research team and can be seen in the Supplementary Materials). 

#### 2.1.3. Sample Size

To ensure that the size of the improvements realized by the intervention are of practical significance, we propose a minimum effect size of Cohen’s *d* = 0.3, which is a small-to-medium effect. A power calculation using this effect size and the proposed analysis plan (see below) was carried out using the program G*Power [35] and indicated that the minimum sample size we require for the study is n = 352. However, due to the difficult living conditions in the proposed recruitment areas (gang violence, long distances from residences to school centres, etc.), we expect a high dropout rate. Therefore, we propose to recruit a total of 480 children as this would allow for slightly more than 25% of the sample to stop participation in the study yet still allow us to maintain sufficient statistical power to detect the target effect size. Furthermore, the figure of 480 represents approximately one-third of 5th grade students attending Fe y Alegría Guatemala across their 46 centres. Thus, we would only need consent from one in every three children to achieve the necessary sample size. This sample size could be reduced if research teams were prepared to look for larger effect sizes. Furthermore, once this protocol is implemented, research groups should consider creating a contingency plan based on the specific conditions they encounter to address potential difficulties in recruitment.

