### 2.4. Procedure

The design of this study protocol follows the guidelines of the CONSORT-revised recommendations for improving the quality of reports of parallel group randomized trials [62]. The study has been pre-registered with the Open Science Foundation. Ideally, children should be randomly allocated to either the control or the experimental group. However, implementation of this protocol requires the use of at least two rooms at the same time, along with a high level of logistical organization in terms of moving the children to their correct rooms for each session. Given the nature of the schools involved, we do not believe it is realistic to expect that these resources will always be available. Hence, we propose that the study will be carried out through a multicentre randomized controlled trial in which entire classes of children will be assigned to either the control or experimental conditions. We note, however, that the members of each class are allocated at random by the school as they enroll, so in this sense, random allocation at the participant level is still somewhat achieved. To minimize potential bias related to school-specific factors, each school will provide [at least] two classes, thus ensuring that each school is represented in both conditions. Efforts should be made to ensure as close to a 1:1 ratio of students between groups as possible. The class designated as the experimental group will receive the intervention. The second group will be made up of the students who will form the control group. A crossover design will be used in which the role of each group is reversed during the following academic year, thus ensuring that each child has the opportunity to benefit from the intervention program. The study will therefore be divided into two blocks (see Figure 2). The first block will occur in year 1 and will consist of a prior and posterior assessment (T1 and T2) of the children’s cognitive and emotional abilities and the implementation of the intervention program in between. The second block will occur in year 2 and will consist of a second intervention, followed by a final assessment (T3), which will occur when the children are in the 6th grade. In this block, the control and experimental groups will change roles. Apart from ensuring that all children may benefit from the intervention program, it will provide an opportunity to determine if there is maintenance of the benefits obtained by the experimental group during the first block. All assessments will be carried out by professional neuropsychologists and educational psychologists, duly trained to administer the assessment tasks by the experts from the research team.

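### The minimum of 352 assumes independent children, but whole classes are allocated, so the claim that 480 recruits keep sufficient power is unsupported for this design

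*Protocol article*

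**What the plan says.** Section 2.1.3 of the protocol article sets the target effect: "we propose a minimum effect size of Cohen’s *d* = 0.3, which is a small-to-medium effect". On method it says: "A power calculation using this effect size and the proposed analysis plan (see below) was carried out using the program G*Power". The calculation "indicated that the minimum sample size we require for the study is n = 352". Recruitment is raised to 480 because "this would allow for slightly more than 25% of the sample to stop participation in the study", which would "still allow us to maintain sufficient statistical power to detect the target effect size". Alpha, sidedness and the power level are not given as numbers.

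Section 2.4 says that allocating individual children would be ideal but is not realistic in these schools, so whole classes go to one condition or the other. On the number of classes it says "each school will provide [at least] two classes", so that every school appears in both arms. Section 2.1.2 names five schools. Section 2.4 adds that schools place children in classes at random on enrolment, and takes this as partly achieving random allocation of individuals.

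Section 2.5 plans an ANCOVA of the post-score with the pre-score as covariate. It mentions multilevel models only as one option for subgroup analyses.

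**The concern.** Children in the same class share a room, staff, sessions and schooling during the trial, so their outcomes are likely to be positively correlated. When whole classes are allocated, that correlation adds to the variance of the difference between arms. A sample size that treats children as independent is then too small for the power it is meant to give.

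The allowance from 352 to 480 does not help, because it is fully spent on dropout. The plan regards 352 completers as enough, and at 352 nothing is left for clustering.

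Two things are at stake. If the analysis accounts for class, a null result may be read as evidence against an effect of d = 0.3 when the trial had less power than stated. If the child-level ANCOVA is run without a class term, the same omission appears as inflated type I error instead. The article is also offered for use by other groups, who may reuse the 352.

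**Working it through.** **Inputs from the article.** d = 0.3; 352 as the analysed minimum; 480 recruited (2.1.3). Whole-class allocation, about 1:1, at least two classes per school (2.4). Five schools (2.1.2). The minimum number of classes is therefore 5 × 2 = 10.

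**Assumptions, because the article gives no value.** Class-level ICC of 0.01, 0.02, 0.05 or 0.10; 10, 20 or 40 equal classes; two-sided 5%. Where baseline credit is shown, the T1–T2 correlation is 0.6 and d is on the unadjusted SD.

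**Step 1: reproduce 352.** Two-sample t-test, noncentral t, d = 0.3, two-sided 5%, 1:1, independent children:

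- 175 per arm: power 0.799
- 176 per arm: power 0.801, so the total is 2 × 176 = 352

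The ANCOVA F-test in G*Power form (f = 0.15, two groups, one covariate) first reaches 80% at 351. One-sided 80% would need 278, and two-sided 90% would need 470. So 352 corresponds to two-sided 5%, 80% power and a design effect of 1.

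**Step 2: the dropout allowance.** 1 − 352/480 = 26.7%, which is the article's slightly more than 25%. Nothing else is built into 480.

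**Step 3: power under class allocation, no baseline credit.** With N completers in k classes of size m = N/k:

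- DE = 1 + (m − 1) × ICC
- SE = √(4 × DE / N), in SD units
- power from the noncentral t with noncentrality 0.3/SE and k − 2 degrees of freedom

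Example, 10 classes and ICC 0.05: m = 35.2; DE = 1 + 34.2 × 0.05 = 2.71; SE = √(4 × 2.71 / 352) = 0.1755; noncentrality 0.3/0.1755 = 1.71; 8 df; power 33%.

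| Classes (m) | ICC 0.01 | 0.02 | 0.05 | 0.10 |
|---|---|---|---|---|
| 10 (35.2) | 57% | 48% | 33% | 22% |
| 20 (17.6) | 69% | 64% | 50% | 37% |
| 40 (8.8) | 75% | 72% | 64% | 54% |

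**Step 4: the same, with baseline credit and school as a stratum.** Multiply the variance by 1 − 0.6² = 0.64 (the same reduction assumed at class level), and use k − 6 df (five schools and one arm contrast). For the example above: noncentrality 1.71/0.8 = 2.14; 4 df; power 37%.

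| Classes | ICC 0.01 | 0.02 | 0.05 | 0.10 |
|---|---|---|---|---|
| 10 | 63% | 54% | 37% | 25% |
| 20 | 86% | 81% | 68% | 52% |
| 40 | 91% | 89% | 83% | 73% |

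**Step 5: if nobody drops out.** All 480 in 10 classes (m = 48), no baseline credit: 66%, 55%, 35% and 23%. In 20 classes (m = 24): 80%, 73%, 56% and 40%.

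**Step 6: a child-level analysis without class.** Type I error is approximately P(|Z| > 1.96/√DE). With 352 children in 10 classes this is about 9% at ICC 0.01 (DE 1.34) and 23% at ICC 0.05 (DE 2.71), against a nominal 5%.

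**The case against.** **Ten classes is a floor, not the design.** This stands. Section 2.4 permits more. Section 2.1.2 puts about 1400 fifth-graders in the five schools; at an assumed 35 per class that is 1400/35 = 40 classes, with 480/40 = 12 participants each. Section 2.1.3 relates 480 to the fifth-graders of all 46 centres instead, so the number of classes cannot be settled from the article. The three layouts are therefore shown side by side. Without baseline credit, all three fall below 80% at 352 completers.

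**The planned pre-score covariate recovers power.** This stands in part. With 40 classes and a correlation of 0.6, power is above 80% up to ICC 0.05. However, section 2.1.3 claims no such gain, 352 does not use it, and with 10 classes it is not enough at any ICC shown.

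**Random class formation and balance within schools keep the ICC small.** This also stands in part. Both limit differences between classes at the start, and the relevant ICC is the one between classes within a school. Neither removes correlation that arises from shared teaching and sessions, and the unit allocated is still the class.

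**A stronger case might be inferred.** A reader could note that exactly two classes in each of five schools give 2⁵ = 32 allocations, so a re-randomisation test could not reach a two-sided p below 2/32 = 0.0625. Section 2.5 plans no such test, and the limit applies only at exactly two classes per school. A reader could also conclude that the 480 must be spread over as many classes as possible. Sessions are delivered to whole classes, and section 2.4 says that rooms and logistics are limited, so that would not be a free change and does not follow from the error in the calculation.

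**Conclusion.** The sample size calculation does not match the allocation. The 352 is an independent-children figure, 480 adds dropout only, and the statement of sufficient power is unsupported for a trial that allocates classes. The direction is certain on the calculation's own terms: any positive ICC puts power at 352 completers below the level on which 352 rests.

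The size is not certain. Across the layouts shown, power at 352 completers runs from 22% to 75% without baseline credit and from 25% to 91% with it. These figures rest on assumed ICCs, numbers of classes and T1–T2 correlation, on equal class sizes, and on an alpha and power inferred from the exact match.

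A reader might infer that the trial cannot detect d = 0.3. The article does not support that: the number of classes is open above 10, a pre-score covariate is planned, and some permitted layouts reach 80%. What is shown is that the stated power is unjustified and could be far lower.

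**What to change.** Redo the calculation in section 2.1.3 for class allocation. State:

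- the number of classes and the number of participants per class;
- a range of class-level ICC within school;
- the T1–T2 correlation assumed, if credit is taken for the covariate;
- degrees of freedom based on the number of classes;
- alpha, sidedness and the power level.

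Then restate the power, or the detectable effect, for 480 recruited and 352 completing. Make clear that this power refers to an analysis that accounts for class.

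The cost is a recalculation, some rewording and a less favourable stated power. The correction requires no extra children and no extra classes. Whether to use more classes is a separate decision, for which the recalculated figures would be the basis.
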